**Figure 2. F2:**
[figure not shown]
Timeline of one block of tests and questionnaires. CPT: continuous performance test; CEC: Conscient Experience Characterization; EEG: electroencephalogram; KSS: Karolinska Sleepiness Scale; MWT: maintenance of wakefulness test; PVT: psychomotor vigilance task; TAP: Test of Attentional Performance; BC5: 5-minute bio-calibration.

### Sleep and Wake Monitoring Setup

Sleep parameters were assessed using ambulatory and laboratory polysomnography coupled with actigraphy. Activity was monitored using a wrist-worn accelerometer (GT9X Link, ActiGraph). Ambulatory polysomnography was performed using an EMBLA Titanium system (Natus; sampling frequency 256 Hz; 16-bit resolution). The montage included 2 EEG channels (Cz and Pz). Laboratory polysomnography was recorded with an Embla NDx amplifier and stored using Natus SleepWorks software (sampling frequency 256 Hz; 16-bit resolution). The montage included at least 2 EOG channels, 1 EMG channel, 6 EEG channels (F4, C4, O2, Cz, Pz, and A1), and 1 ECG channel.

While awake, participants were equipped with a gel-based active electrode system for EEG (Acticap Slim, Brain Products) connected to a compact wireless EEG amplifier LiveAmp (Brain Product: 24-bit resolution). The montage included 8 EEG derivations, namely Fz, Cz, Pz, C4, O2, C3, O1, and P3, and 4 vertical and horizontal EOG. All signals were acquired using a sampling frequency of 500 Hz.

### Description of the Tests

Introspective sleepiness was investigated through the Karolinska Sleepiness Scale (KSS), a subjective scale assessing the level of sleepiness during the past 10 minutes [43]. Participants are required to rate their ability to maintain wakefulness on a Likert scale (from 1 = “perfectly awake” to 9 = “severely somnolent, cannot stay awake”). This score is known to correlate well with EEG measurements and cognitive and behavioral performances linked to the candidate’s ability to maintain wakefulness [44].

The ability to stay awake under sleep-promoting conditions was monitored through the MWT, which is considered the gold standard in the measurement of manifest sleepiness [18,45]. The MWT is a 40-minute trial during which the participant is in a comfortable position in bed, in a quiet, dimly lit room. At the beginning of each trial, the candidate is instructed to stay awake and combat against sleep, to keep their eyes open, and to look straight ahead, without looking at the light. During the test, visual analysis of the polysomnographic recording allows for monitoring the participant’s state, and the test is stopped when unequivocal sleep is detected (defined by 3 consecutive epochs of stage N1 sleep or 1 epoch of any other sleep stage, according to the American Academy of Sleep Medicine (AASM) recommendations [46]).

Driving performance was assessed during a driving simulation procedure, as it provides an ecological approach that is commonly used to assess the effects of sleepiness on complex cognitive performance and safety, using the fixed-base INRETS-MSIS SIM2 (Institut National de Recherche sur les Transports et leur Sécurité — Modélisations, Simulations et Systèmes d’Information pour la Sécurité — Simulateur version 2; National Institute for Transport and Safety Research — Modeling, Simulation, and Information Systems for Safety — Simulator version 2) driving simulator [47]. In healthy individuals, this simulator has been shown to effectively assess nocturnal driving impairment in a dose-response design, considering extended wakefulness and driving duration, compared to real driving conditions [48]. The driving simulator is composed of a computer and a video game steering wheel with no force feedback applied. The participant’s head is positioned at 60 cm in front of the screen. The resolution of the visual scene was 1024×768 pixels, and the update rate was 60 Hz. The simulator generates a highway driving scenario on a 19-inch screen. The car’s speed was fixed by the experimenter at 130 km/h, and participants were instructed to drive in the center of the right lane. The test lasts for 20 minutes, during which the participant must maintain the car’s trajectory on a monotonous 2-lane highway (reconstruction of the French A62 highway, without any scenery or vehicles).

To evaluate the impact of sleepiness on cognitive performance of increasing complexity, we included 3 tasks ranging from basic attentional measures to more demanding cognitive functions. First, the participants completed the Psychomotor Vigilance Task (PVT), a widely used and validated tool for quantifying manifest sleepiness, particularly through its effects especially on sustained attention and somewhat less on vigilance [18]. The test consists of a one-choice serial reaction time task and was conducted using PC-PVT software (Biotechnology HPC Software Applications Institute), a freely available package for PVT testing, analyzing, and visualizing on a PC, whose performance is comparable to the PVT-192, the gold standard for measuring PVT [49]. The PC-PVT software [50] was installed on a desktop computer running under Windows 10 and equipped with a mouse. The test session lasts 10 minutes, during which a visual stimulus randomly appears on a screen, with interstimulus intervals varying from 2 to 10 seconds. The participant is asked to react as quickly as possible (by a mouse click) to make the stimulus disappear.

The Conners continuous performance test II (CPT-II) is a Go/No-Go task that evaluates the participant’s ability to maintain sustained attention and to discriminate relevant stimuli [51]. The test assesses inhibitory control, which is known to be highly sensitive to excessive daytime sleepiness [52-54]. The CPT (continuous performance test) paradigm is based on monitoring and responding to regular targets (here, all alphabet letters except the “X”), while withholding the response to a specific infrequent nontarget (letter “X”). CPT software (Multi-Health Systems Inc, version 5.2) was installed on a desktop computer running under Windows 10 and equipped with a keyboard. The test session lasts for 15 minutes, and the participant is asked to push the space bar when any letter is displayed on the screen, except for the letter “X” (target stimulus).

The Vigilance Test of Attentional Performance (TAP) is a rarely used animated line test, which measures the ability to focus and to maintain mental effort and vigilance on a monotonous task during a 30-minute period [55]. The test displays a horizontal line going up and down on a screen at an irregular speed, and from time to time, this line oscillates with a greater amplitude. TAP Vigilance (Psytest) software was installed on a desktop computer running under Windows 10 and equipped with a specific external response button. The participant is asked to push the response button when they notice a difference in the line oscillation amplitude (target).

Finally, mind-wandering during completion of the test was assessed through a subjective scale, the Conscient Experience Characterization (CEC) [56]. At the end of the cognitive tests, participants were asked to rate their focusing level during the previous task, using a scale of five options: (1) fully focused (attention and thoughts entirely dedicated to the task), (2) focus interference related to the task (attention and thoughts distracted by task characteristics or by their performance), (3) external distraction (attention and thoughts distracted by environmental stimuli with no relation to the task), (4) mind wandering (not focused, with thoughts disconnected from the task or the environment), and (5) empty mind (not focused, without any particular thoughts).

### Experimental Session 1: Fragmented Sleep

This session lasted for 3 consecutive nights and days, during which sleep was recorded. In order to induce sleep pressure on day 3, the third night was fragmented (with 2 imposed wake-ups, during which attentional and vigilance tests were carried out). Three blocks of behavioral tests were conducted during the third day (Figure 1A). One block of tests is 4 hours long and includes, in a fixed order, a driving simulation, cognitive tests, evaluation of sleep pressure, and self-assessments of drowsiness and mind-wandering, while continuous EEG is recorded (Figure 2).

The detailed schedule of days and nights is organized as follows:

Night 1: In the evening before the first night, the participants arrived at the laboratory to be equipped with Ag-AgCl electrodes (2 EEG derivations: Cz and Pz, connected to the EMBLA Titanium) to measure their sleep quantity and quality. They returned home for the first night, went to sleep, and woke up according to their usual schedule.Day 1: After waking up and removing the sleep recorder, the participants carried out their usual activities throughout the day before returning to the laboratory in the evening, where training for the cognitive tests and driving simulation was provided.Night 2: The participants were equipped with Ag-AgCl electrodes (6 EEG derivations: F4, C4, O2, Cz, Pz, A1, 1 EMG, 2 EOG, and 1 ECG) connected to the Embla NDx amplifier to measure their sleep quantity and quality. They spent the night in the laboratory, went to sleep, and woke up according to their usual schedule.Day 2: After waking up, the participants either stayed in the laboratory or went to their regular activities before returning in the evening.Night 3: The participants were re-equipped with polysomnographic sensors (as during night 2) and went to bed by midnight. They were awakened twice during the night (2 hours and 4 hours after bedtime) for 30 minutes, during which they underwent the PVT and CPT tests to measure their vigilance along with their ability to maintain sustained attention.Day 3: After waking up at 7 AM, the equipment was removed, and the participants were equipped with a gel-based active electrode system for EEG. The participants underwent 3 test blocks. Block 1 occurred from 8 AM to noon, block 2 from noon to 4 PM, and block 3 from 4 PM to 8 PM After the last block, the EEG helmet was removed, and the participants either stayed in the laboratory for a recovery night or left the hospital, if accompanied, with a recommendation to go home for a recovery night.

### Experimental Session 2: Sleep Deprivation

This session lasted for 4 consecutive nights and 3 days, during which sleep was recorded. During the second day, the participants began a series of six 4-hour test blocks, lasting 24 hours and leading to a total sleep deprivation during the third night. On the third day, the participants had a morning recovery sleep period (4 hours) and began a new night of total sleep deprivation with a series of three 4-hour test blocks during the fourth night (Figure 1).

The detailed schedule of days and nights is organized as follows:

Night 1: In the evening before the first night, the participants entered the laboratory to be equipped with Ag-AgCl electrodes (2 EEG derivations: Cz and Pz) connected to the EMBLA Titanium to measure their sleep quantity and quality. They returned home for the first night, went to sleep, and woke up according to their usual schedule.Day 1: After waking up and removing the sleep recorder, participants carried out their usual activities throughout the day before returning to the laboratory in the evening.Night 2: The participants were equipped with Ag-AgCl electrodes (6 EEG derivations: F4, C4, O2, Cz, Pz, A1, 1 EMG, 2 EOG, and 1 ECG) connected to the Embla NDx amplifier to measure their sleep quantity and quality. They spent the night in the laboratory and went to bed by midnight.Day 2 and Night 3: After waking up, the equipment was removed, and the participants had breakfast before being equipped with a gel-based active electrode system for EEG. Then, the participants completed six 4-hour test blocks. Block 1 occurred from 8 AM to noon, block 2 from noon to 4 PM, block 3 from 4 PM to 8 PM, block 4 from 8 PM to midnight, block 5 from midnight to 4 AM, and block 6 from 4 AM to 8 AM. After the last block, the EEG helmet was removed.Day 3: The participants underwent a morning recovery sleep period (from 9 AM to 1 PM) during which they were equipped with the Ag-AgCl electrodes and sleep recorder, as described for night 2, to measure their sleep quantity and quality. After waking up, sensors were removed, and the participants remained in the laboratory without sleeping during the afternoon.Night 4: The participants were re-equipped with the gel-based active electrode system for EEG and wireless EEG amplifier, as described for Day 2 and Night 3, and underwent a new series of three 4-hour test blocks. Block 1 occurred from 8 PM to midnight, block 2 from midnight to 4 AM, and block 3 from 4 AM to 8 AM After the last block, the EEG helmet was removed.Day 4: The participant either stayed in the laboratory for a 5-hour recovery sleep or left the hospital, if accompanied, with a recommendation to plan a sleep recovery night at home.

### Protocol Assistant

Protocol Assistant is a software tool developed by Physip to manage the timeline of the various behavioral tests and questionnaires during the 4-hour block and to ensure synchronization with the EEG and EOG acquisition performed by a Brain Products amplifier (ie, LiveAmp). It is designed to provide event markers (start and end of each test) with a time precision of approximately 0.1 seconds, without requiring any programming skills. Additionally, it allows for the collection and timestamped recordings of responses to self-assessment questionnaires (KSS and CEC) and any comments the experimenter may make during the experiment.

After a preliminary configuration phase, during which the timeline for tests and questionnaires is set once and for the 4-hour block, the software has to be launched for each acquisition. It opens a graphical interface with windows on 2 separate screens (one for the experimenter and one for the participant), enabling the protocol to be run and the test and questionnaire instructions to be presented to the participant, in written and audio form, while managing the acquisition of EEG signals realized by the EEG amplifier.

The software automatically adds time markers on the fly to the protocol steps and enables the experimenter to follow the progress of the protocol via a graphical timeline and via the list of steps, to visually monitor the tracings in real time, insert customizable predefined event markers, and interrupt or resume the progress of the protocol.

### Outcome Measures

#### Primary Outcome Measure

The primary outcome measure corresponds to the OSS score, which relies on the analysis of electrophysiological variables to assess the instantaneous drowsiness state, corresponding to the participant’s level of sleepiness. The OSS score, ranging from 0 (full alertness) to 4 (very drowsy), is assigned every 20 seconds, based on specific EEG activity (amount of beta, alpha, and theta waves) observed simultaneously in 2 regions of the brain during each epoch, and accompanied by distinct eye blinks and movements (normal or slow). An OSS score of 0 corresponds to continuous beta activity, with no alpha or theta activity and no slow eye movements. In contrast, an OSS score of 4 is characterized by the presence of alpha and/or theta rhythms for more than 10 cumulative seconds, associated with slow eye movements.

The OSS was scored both manually, by a trained experimenter—based on EEG (Fz, Cz, Pz, C4, O2, C3, O1, and P3) and EOG (vertical and horizontal) recordings—and automatically, by the MEEGAWAKE algorithm—based on EEG (Cz and Pz)— every 20 seconds throughout all behavioral tests, to reflect the spontaneous drowsiness states.

The MEEGAWAKE algorithm uses data-driven criteria to cope with interindividual variability. After an initial artifact rejection step relying on detecting both temporal and frequential abrupt variations or nonphysiological behavior, the analysis step aims to determine recording-specific thresholds based on EEG power ratios in the usual frequency bands. In addition to this frequency analysis, a temporal localization of EEG events is performed to analyze burst activity. Based on the results of this analysis, the final step is to classify the 20-second epochs into OSS drowsiness states.

During MWT, sleep onset is defined as the start of the first epoch scored 3 or 4. OSS sleep latency (OSS latency) is defined as the time from lights out until the start of the first epoch scored as 3 or 4 (expressed in minutes).

#### Secondary Outcome Measures

The secondary outcome measures are the following: resting state EEG, longer resting state EEG, objective sleep quantity and quality, objective measurement of manifest sleepiness, driving performance, cognitive performance, and subjective sleepiness and mind wandering.

Resting state EEG, recorded through bio-calibrations, is a simple procedure in which participants are placed in a quiet room and asked to relax while looking at a picture on the wall, to keep their eyes open for 1 minute, refraining from blinking as much as possible, and then close their eyes for 1 minute, without moving (BC2). EEG and EOG channels are recorded continuously during bio-calibrations. In the preprocessing step of the signal analysis, standard signal processing techniques will be used, including notch filtering to remove power-line interference and bandpass filtering to isolate specific frequency subbands. The EEG data will be segmented into 4-second epochs to minimize the effects of nonstationarity in longer signal segments. Spectral power across different EEG frequency subbands and the frequency centroid will be computed for each channel under both eyes-open and eyes-closed conditions. To mitigate the influence of outliers, the median spectral power across epochs within each session will be used. EEG signal processing will be performed using the Python (Python Software Foundation) MNE toolbox (magnetoencephalography and electroencephalography in Python). Following preprocessing, feature vectors representing each session will be constructed, comprising multiple EEG-derived features. These feature vectors will then serve as inputs for a machine learning model to identify the most informative features for distinguishing participants’ levels of drowsiness, cognitive, and driving performances as quantified by the different tests conducted after the bio-calibrations.

Longer resting state EEG, recorded through a longer bio-calibration, is a procedure that remains the same as described for BC2, but here the participants are asked to keep their eyes open for 5 minutes (BC5). During the 5 minutes with eyes open, the Fz signal is analyzed in 2-second epochs, each characterized by features including the signal magnitude and spectral power (Fast Fourier Transform, Hanning window) in the frequency bands delta (0‐4 Hz), theta (4‐8 Hz), alpha (8‐12 Hz), sigma (12‐16 Hz), and beta (16‐50 Hz). After automatic artifact and blink removal using both temporal and frequential criteria, the spectral power of the artifact-free Fz signal will then be computed in the 6‐9 Hz band [57] for each 2-second artifact-free epoch. The resulting distributions of spectral power values will then be characterized by their mean, SD, and median. The mean spectral power will be the result of BC5. To compare values between individuals while controlling for interindividual variability, a participant’s test values are normalized by their median.

Objective sleep quantity and quality, measured through polysomnography recordings and analyzed by ASEEGA software (Physip), are based on an automated analysis of a single EEG channel (Cz-Pz) using a combination of multiple signal processing and classification techniques [58-60]. The preprocessing phase notably aims to adapt the analysis criteria to cope with EEG interindividual variability. The analysis step uses both frequency and temporal techniques to retrieve numerous 30-second-long and 1-second-long features as well as performing the detection of several sleep microstructural events. The classification phase then reduces and summarizes this information by scoring sleep EEG into conventional sleep stages using artificial intelligence techniques, such as pattern recognition and fuzzy logic. This method was validated in healthy individuals and demonstrated high agreement with visual scoring realized by an experienced scorer, between 82.9% and 96%, depending on the number of vigilance stages considered, allowing its application in several research studies [59,60]. Classical sleep parameters like the total sleep time (TST: the sum of all sleep stages, expressed in minutes), sleep onset latency (SOL: the time, in minutes, from lights out to the first recorded epoch of any sleep stage, N1, N2, N3, or Rapid Eye Movement), sleep efficiency (calculated as the ratio of TST to total time in bed, multiplied by 100), wake after sleep onset (calculated as the total time in bed minus the TST), and time spent in stages N1, N2, N3, and Rapid Eye Movement (expressed as a percentage of TST and in minutes) will be computed. Objective sleep quantity and quality will also be measured through actigraphy recordings and analyzed by ActiLife software (ActiGraph) using the Cole-Kripke algorithm. The sleep outcomes calculated were TST (minutes), SOL (minutes), and sleep efficiency (%).

Objective measurement of manifest sleepiness will be assessed during the MWT and analyzed visually by an experienced technician according to the AASM criteria [61]. Objective sleepiness is quantified by the SOL (minutes), defined as the time from lights out to the start of the first epoch of any sleep stage (N1, N2, N3, or rapid eye movement). If the patient succeeds in staying awake during the entire duration of the test, the SOL is set to 40 minutes.

Driving performance, assessed using a driving simulator, is quantified by the variability of the car’s lateral position (standard deviation of lateral position [SDLP; cm]), indicating weaving of the car, and the number of inappropriate crossings of lateral highway lane markers (Inappropriate Line Crossing).

Cognitive performance is assessed using the PVT, the CPT, and the TAP. For the PVT, outcome measures include mean reaction time (RT; milliseconds), the fastest and slowest 10% of RTs, and the number of lapses (RT>500 ms). For the CPT, outcomes consist of the mean RT (measuring the response execution process), the number of omissions (failure to respond to target stimuli), and commission errors (responses given to nontarget stimuli). For the TAP, outcomes include mean RT and the number of omissions (missed targets).

Subjective sleepiness and mind wandering are assessed using the KSS and the CEC, respectively. The outcome measure for both is the score on the corresponding scale.

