#### OSS Criteria Accuracy Evaluation

Considering that the collected data consist of either continuous linear data, counts, or proportions, it is very likely that some of the data will not follow a normal distribution. Therefore, the use of parametric tests may be compromised. Moreover, our outcomes are measured repeatedly over time and may be highly dependent on interindividual variability. Thus, we will use a generalized linear mixed model to explore our first main objective, with relevant interindividual data incorporated into the model if needed (including patient ID, age, gender, daydreaming frequency, chronotype, and sleep history).

Using such models, OSS and MWT sleep onset latencies will be compared over time in order to determine whether OSS criteria can accurately detect drowsiness compared to the MWT.

As a second step, behavioral performance based on the OSS score will be assessed to determine whether instantaneous drowsiness states, identified by OSS, can detect momentary functional impairments. The evaluation of OSS temporal accuracy will be conducted by selecting OSS scores greater than 0 at a time T (20-second epoch), surrounded by lower score values (at T-20 seconds and T+20 seconds) [26]. Behavioral outcomes will then be compared using a generalized linear mixed model between T-20 seconds, T, and T+20 seconds of selected OSS scores.

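### Wake after sleep onset is defined as time in bed minus total sleep time, which is total wake in bed and includes sleep onset latency

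*Protocol article*

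**What the plan says.** The paragraph on objective sleep in Secondary Outcome Measures defines four linked polysomnography parameters:

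- "total sleep time (TST: the sum of all sleep stages, expressed in minutes";
- sleep onset latency (SOL), which is "the time, in minutes, from lights out to the first recorded epoch of any sleep stage";
- "sleep efficiency (calculated as the ratio of TST to total time in bed, multiplied by 100";
- and, as the fourth parameter and the one at issue here, "wake after sleep onset (calculated as the total time in bed minus the TST".

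The article does not say when time in bed begins. No other section gives a different definition of wake after sleep onset (WASO) or starts time in bed at sleep onset. WASO is listed for polysomnography only; the actigraphy outcomes are TST, SOL and sleep efficiency.

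Sleep windows differ between nights. On Night 1 of each session participants slept at home: "They returned home for the first night, went to sleep, and woke up according to their usual schedule". Session 2 also has a window common to all: "The participants underwent a morning recovery sleep period (from 9 AM to 1 PM". In Session 1 Night 3, with bed by midnight and waking at 7 AM, sleep was interrupted: "They were awakened twice during the night (2 hours and 4 hours after bedtime) for 30 minutes".

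OSS Criteria Accuracy Evaluation names the interindividual data that may enter the mixed model if needed: "including patient ID, age, gender, daydreaming frequency, chronotype, and sleep history". Predictive Models Using Resting State EEG makes a similar list optional for the classifiers.

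**The concern.** The name and the formula describe different quantities. WASO is meant to measure sleep maintenance, that is, wake after the participant has first fallen asleep. Subtracting only TST from time in bed leaves the initial latency inside the result. A participant who takes long to fall asleep and then sleeps soundly would be reported as having broken sleep, and the same minutes would appear in two listed parameters, SOL and WASO.

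The formula also ties WASO to sleep efficiency by algebra, so the listed parameter gives no separate information on maintenance beyond time in bed and efficiency. The values would not be comparable with WASO counted from sleep onset. If WASO were entered in a model together with SOL, TST or efficiency, the inputs would be mechanically dependent.

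**Working it through.** The plan gives no numerical WASO figure to reproduce, so the check is algebraic and uses the article's own definitions. Write TIB for time in bed, SE for sleep efficiency, and W for wake after the first sleep epoch, including any final wake before rising.

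**Step 1: what the formula contains.** If TIB starts at lights out, TIB = SOL + W + TST. Then TIB − TST = SOL + W, and the excess over W is SOL. If TIB starts p minutes before lights out, TIB = p + SOL + W + TST, and the excess is p + SOL.

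**Step 2: link with sleep efficiency.** SE = 100 × TST/TIB gives TST = TIB × SE/100. So TIB − TST = TIB × (1 − SE/100). This holds wherever TIB starts, provided both parameters use the same TIB.

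**Step 3: numbers.** The article gives no SOL or W values, so these are assumed: SOL 5, 15 or 30 min, and W 10 or 30 min. TIB is 240 min (the 9 AM to 1 PM window, if fully used), 420 min (midnight to 7 AM, if bedtime is exactly midnight) or 480 min (assumed). TIB is taken to start at lights out. Five of the 18 combinations, in minutes except SE:

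| TIB | SOL | W | TST | SE (%) | Plan's WASO | TIB × (1 − SE/100) | Excess over W |
|---|---|---|---|---|---|---|---|
| 240 | 5 | 10 | 225 | 93.75 | 15 | 15 | 5 |
| 240 | 30 | 10 | 200 | 83.33 | 40 | 40 | 30 |
| 420 | 15 | 30 | 375 | 89.29 | 45 | 45 | 15 |
| 480 | 15 | 10 | 455 | 94.79 | 25 | 25 | 15 |
| 480 | 30 | 30 | 420 | 87.50 | 60 | 60 | 30 |

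Both identities hold in all 18. The relative overstatement is SOL/W. On this grid it runs from 5/30 = 17% to 30/10 = 300%, so any single percentage reflects the values chosen.

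**Step 4: how close to sleep efficiency.** A simulation assumed SOL with mean 15 min and W with mean 24 min (both gamma, shape 2).

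| TIB | Correlation with SE, plan's WASO | Correlation with SE, SOL removed |
|---|---|---|
| fixed at 240 min | −1.00 | −0.85 |
| mean 460, SD 40 min | −0.98 | −0.83 |

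Apart from the exact −1.00 at fixed TIB, these correlations depend on the assumed distributions. The identities in Steps 1 and 2 do not.

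**Step 5: Session 1 Night 3.** Read the two awakenings as 30 min each, which fits a 10-min PVT plus a 15-min CPT (25 min). If TIB is 420 min and includes them, a participant asleep for every permitted minute has TST = 420 − 60 = 360. That gives WASO = 60 min and SE = 360/420 = 85.7%. Subtracting SOL (here 0) would leave the same 60 min. This is therefore a separate matter of how time in bed is counted, not a result of the WASO formula.

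**The case against.** The best case on the other side is that this is a slip in one phrase about a minor descriptor. WASO appears once, among several conventional sleep parameters, within one of seven secondary outcome groups. It enters neither the comparison of OSS and MWT latencies nor the SDLP endpoint of the classifier. SOL, TST and efficiency are defined separately and are unaffected. If time in bed starts at lights out, a reader can recover true WASO by subtracting the reported SOL. All of this stands and limits the weight of the point. It does not make the stated formula right.

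Three stronger readings are tempting, and the article does not support them.

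- A reader might infer that WASO simply restates sleep efficiency. That is exact only where time in bed is the same for everyone. On usual-schedule nights time in bed varies, and WASO as written is fixed by efficiency and time in bed together.
- A reader might infer that the error enters both main analyses through sleep history. That covariate is conditional in the mixed model and optional in the classifiers, and neither section defines it as WASO. No stated model contains WASO.
- A reader might infer that Night 3 will show an artificial 60 min of WASO. That requires the test periods to count as time in bed, which the article does not say. The tests run on desktop computers, which fits being out of bed, and bedtime is given as by midnight, not at midnight.

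**Conclusion.** The concern holds as a definitional error: the quantity described is total wake time in bed, not wake after sleep onset. The excess equals SOL in every recording if time in bed starts at lights out, so 5 to 30 min under an assumed SOL of 5 to 30 min. It equals SOL plus the time in bed before lights out if time in bed starts earlier. The identity with time in bed and sleep efficiency is exact and needs no assumption beyond a common time in bed.

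The reach is one secondary polysomnography descriptor. The models are affected only if WASO is chosen as a sleep-history covariate. The primary OSS and MWT comparison does not use it. The Night 3 figures are conditional on an unstated convention and are only a side point.

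**What to change.** Compute WASO as the wake epochs between the first sleep epoch and the end of the sleep period, and state whether that period ends at rising. If it does, this equals the time from lights out to rising, minus SOL, minus TST. The epoch count is the safer wording, because it does not depend on when time in bed is taken to start. Alternatively, keep the present formula and rename the quantity total wake time in bed.

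State when time in bed begins. For Session 1 Night 3, say whether the two imposed awakenings count as time in bed; if they do, report that imposed wake separately from spontaneous WASO. If sleep-history covariates are drawn from these parameters, avoid entering ones that determine each other.

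The cost is one changed definition and a recomputation from existing sleep scoring. No new data are needed. The article reports database lock in June 2025 with analysis still ongoing, so the change can be made before results are reported and recorded as a correction.
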